### Informed consent

Patients who meet inclusion criteria will be informed of the nature of the study, by the recruiting EP. A description of the trial will be provided to the patients (written and verbal information) and discussions on the information provided, before they give their oral consent to the research investigator. The legal requirement in the country for the study is an oral consent to be given. A third party will act as a witness (Nurse or EP). The oral consent will be recorded by the witness in the medical record.

### Allocation

Participants will be randomly allocated to either study group: PT or no-PT with a ratio 1:1. A SAS program will be used to produce a permuted blocks randomization plan with varying block sizes. This program will be performed by a statistician of the DRI of the University Hospital of Nantes. The randomization will be not stratified.

The investigator can allocate the study group of the included patients using a web browser by connecting to ENNOV Clinical Software: this is a secure, computer-generated, interactive web-response system available at: https://nantes-lrsy.ennov.com/EnnovClinical/login.

### Blinding

It will not be possible to keep physiotherapists of the ED and patients blinded, due to the nature of the study.

### Intervention

Only participants of “PT-group” will receive a delivery of PT within ED, composed by a motor assessment as recommended by French National Guideline [33] and a daily session of rehabilitation until discharge from the ED. The ED physiotherapist will report the results of the examinations and exercises, into the patients’ medical record. In addition, the ED physiotherapist will provide a recommendation regarding the patient’s orientation (discharge/hospitalization). This information will be accessible to the EP to assist in making the final decision regarding patient’s orientation.

#### Motor assessment

A battery of clinical tests are recommended to better estimate balance, motor capacities and risks of falls in older populations, overcoming the psychometric limitations of one test used in isolation [34]. These tests are also chosen in order to be the most suitable in context of emergency medicine, optimizing: the delivery format, the training and time required for administration and the need of assistive devices. The battery of tests lasts 30 minutes to be delivered to a patient aged 75 years and over in context of ED. Before each test, the assessor (ED physiotherapist) will provide instructions and show how to perform the test. One repetition of each test will be used. The Table 1 details the procedures of each test.

**Table 1 pone.0303362.t001:** Clinical assessments and exercises used during PT intervention in ED (patient ≥ 75 years).

Name of the Assessment	Description	Threshold for initiating exercises within the ED	Example of exercises
Unipedal Balance Test—UBT [35] Duration: 2 minutes	The patient is asked to stand barefoot on the limb of his choice, with the other limb raised so that the raised foot was near but not touching the ankle of their stance limb. Each patient is asked to focus on a spot on the wall at eye level in front of him/her, for the duration of the eyes open test. Prior to raising the limb, the patient is instructed to cross his arms over the chest. The investigator uses a stopwatch to measure the amount of time the patient was able to stand on one limb. Time starts: when the patient raised the foot off the floor. Time ends: when the patient either: (1) used his arms (ie, uncrossed arms), (2) used the raised foot (moved it toward or away from the standing limb or touched the floor), (3) moved the weight-bearing foot to maintain his balance (ie, rotated foot on the ground), (4) a maximum of 45 seconds had elapsed, or (5) opened eyes on eyes closed trials.	< 5 sec	Unipodal stance exercise (each limb) with eyes opened/closed, for a duration of 6 sec
Romberg test [36] Duration: 2 minutes	The patient stands on the floor, preferably with shoes off, feet together. The patient is asked to maintain the position with eyes open and then closed. The investigator uses a stopwatch to measure the amount of time the patient (upper limit typically = 30 seconds) is able to maintain the position with eyes open then retested with eyes closed. Prior to raising the limb, the patient is instructed to cross his arms over the chest. The Romberg test is positive when the patient is unable to maintain balance with their eyes closed. Losing balance can be defined as increased body sway, placing one foot in the direction of the fall, or even falling.	Positive	Transfer from supine to seated position, seated to bipodal stance
Tinetti Performance Oriented Mobility Assessment Duration: 10 minutes	For testing the balance abilities: The patient is asked to sit, to stay, to rise up and stay standing from an armless chair. Then, the patient is asked to turn 360° and sit back down. The investigator looks at how the patient rises and sits down, stays upright particularly when eyes are closed or when getting pushed against the sternum. For testing the dynamic balance: the patient is asked to walk a few metres (15 feet) at normal speed, to turn and walk back at a speeder (but safe) velocity, and to sit back on the chair. The investigator looks at the quality of the steps (length and height), the symmetry and continuity of the steps, and to the rigidity of the trunk. Brace, cane, walker or any device used to walk can be used during the test. Balance (/16) and gait (/12) scores are summed to 28. The lower the score, the higher the risk of falling.	19	Balance exercise with external perturbation
Time Up and Go Test—TUG [37] Duration: 5 minutes	The patient is sitting in a chair. The patient is asked to stand up (command “go”) and walk forward 3 metres (10 feet), to turn around at the foot mark on the floor and to walk back to the chair. The investigator uses a stopwatch to measure the amount of time between the command to start, till the buttocks touch the chair. Brace, cane, walker or any device used to walk can be used during the test.	> 20 sec	Walking with assistive device related to deficiencies + typical pattern of gait
Stop Walking When Talking test—SWWT [38] Duration: 5 minutes	The patient is walking down in the ED service (in a corridor) under the supervision of the investigator. The supervisor observes whether the patient stops or not walking when a conversation in engaged by the investigator.	Positive	Gait with double task (counting, speaking…)
Ankle range of motion in dorsiflexion Duration: 5 minutes	The patient is supine with knee flexed at 90° and foot in neutral position of inversion/eversion. The investigator stabilizes tibia and fibula to prevent hip/knee compensations. Using a goniometer centered at the bottom center of the lateral malleolus, with proximal arm positioned in reference of fibula head and the distal arm in reference to the 5^th^ metatarsal, respectively, the angulation in maximal passive dorsiflexion angle, is measured at the angle corresponding to the onset of pain	< 5°	Ankle mobilisation/ calf stretches

The One Leg Balance Test (OLBT) also named one-leg balance test or single-balance test will characterize static aspects of standing balance. OLBT is a valid measure for explaining important dimensions in elderly such as frailty, self-sufficiency in activities of daily living, gait performance, and fall status [35,39,40]. For that purpose, the investigator measures the amount of time the patient is able to stand on one limb. We will use the procedures of OLBT described by Springer et al [35]. A duration of a one limb stance <5 sec with eyes opened will be judged as abnormal [33].

The Romberg test will characterize the aspect of balance control due to proprioceptive sensibility [36]. The investigator measures the amount of time the patient is able to maintain balance eyes open or closed. The Romberg test is positive when the patient is unable to maintain balance with their eyes closed. Losing balance can be defined as increased body sway, placing one foot in the direction of the fall, or even falling.

The Tinetti Performance Oriented Mobility Assessment (TPOMA) will be used to characterize balance and gaits impairments during daily activities for elderly populations [41]. The test is composed by two short sections examining the static balance abilities in a chair and standing, and the gait capacities.

The Time Up and Go test (TUG) will be used to assess mobility, balance, and walking ability [37]. TUG may also assist clinicians to identify patients at risk of falling. [42] The investigator measures the amount of time it takes for a patient to stand up, walk 10 ft, walk back and sit down to the same chair. The faster the test, the lower the risk of falling. A TUG>20 sec is associated as a high risk of falling.

The Stop Walking When Talking test (SWWT) will be used to assess the ability to successfully dual task walking with talking. This test examines the relationship between changes in gait and attention-demanding task performance. The SWWT test is also used for fall predication in elderly populations [43]. The test is positive when the patient stops walking when engaged in conversation.

Ankle flexibility in dorsiflexion will be measured through a manual examination of ankle joint range of motion in dorsiflexion, due to the necessity of adequate range motion for executing balance strategies in order to prevent a fall [44].

#### Rehabilitation exercises

A rehabilitation session will be delivered after the clinical assessment, and will last 30 minutes. Different types of exercises will be used, including verticalization exercises, mobility/balance work (eyes open/closed), gait exercises (with or without an assistance device), patient education, tailored to each patient’s needs. The types of exercises are described in Table 1. Note that rehabilitation exercises will be provided/adjusted to patient’s condition each day, until the discharge of ED unit.

### Outcomes

All outcomes, measurement time points and aggregations methods are described in Table 2.

**Table 2 pone.0303362.t002:** Summary of outcomes.

Variable	Aggregation method	
	‘PT-group’	‘no PT-group’
Age, at ED admission	mean (SD)	
Gender		
female	n (%)	
male	n (%)	
Emergency Severity Index Level		
1	n (%)	
2	n (%)	
3	n (%	
4	n (%)	
5	n (%)	
Average	mean (SD)	
Primary diagnosis		
Toxicologic	n (%)	
Traumatic	n (%)	
…	n (%)	
Orientation, at discharge from ED (EU patients)		
Return to home	n (%)	
Hospitalization	n (%)	
SSHU	n (%)	
Orientation, at discharge from ED (OU patients)		
Return to home	n (%)	
Hospitalization	n (%)	
Number of falls, within 7 days	n (%)	
Average	mean (SD)	
Number of re-visits to ED for falls, within 7 days	n (%)	
Average	mean (SD)	

Abbreviations: ED: Emergency department; EU: Emergency Unit; OU: Observation Unit; PT: physiotherapy; SD: Standard deviation.

Characteristics of patients at admission to ED will include: gender and age, emergency severity index level, and primary diagnosis.

The primary outcome will be the patient orientation at discharge from the ED according to the defined pathways: return to home (after ERU or SSHU), hospitalization (after ERU or SSHU) or SSHU (after ERU).

The secondary outcomes will be: the length of stay at the ED, or hospital (LOS-ED, LOS-hos) calculated as the duration between admission and discharge from the ED and hospital; the number of re-visits to ED for fall complaints (within 7 days). These outcomes will be found from the medical record of the patient. In addition, a study investigator will call the patient (phone) after 7 days to collect the number of falls since discharge from ED (follow-up).

At the end of the study, the ED medical staff will be asked about their experiences in providing PT within ED: for elderly populations, and in general context. To gather this information, a satisfaction questionnaire containing 4 closed-ended questions, and 2 open-ended questions (for general comments) will be sent electronically via email (Fig 4).

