## Abstract

The use of physiotherapy (PT) in the hospital emergency department (ED) has shown positive results including improvements in patient waiting time, treatment initiation, discharge type, patient outcomes, safety and acceptability of the intervention by medical staffs. These findings originate from studies that primarily focus on musculoskeletal and orthopaedic conditions. Despite a significant number of people visiting the ED, there is a shortage of literature evaluating PT in the ED for elderly populations. The objective of this study is the evaluate the effect of delivering PT in the ED (versus no delivery) in patients aged 75 and over with ‘falls’ complaints. The main objective is the evaluate the effect on the discharge disposition (discharge home, hospitalization). Secondarily, we will evaluate the effect delivering PT on patient-length of stay, the number of falls at 7 days after admission to the ED, changes between the initial and final medical decision regarding patient orientation, and medical staff satisfaction. This study will follow a prospective longitudinal design involving participants aged 75 years and over. We plan to recruit a total n = 336 patients admitted to the ED with a ‘fall’ chief complaint. After consent, participants will be randomized into either the ‘PT-group’ (receiving a prescription and execution of PT within the ED), or to the ‘no-PT group’ (no delivery of PT within the ED). The PT intervention will involve a standardized assessment of motor capacities using validated clinical examinations, and the delivery of rehabilitative exercises based on individual needs. Outcomes will be recorded from the patient’s medical record, and a phone call at 7 days. A questionnaire will be sent to medical staff. The results of this study will help to determine whether PT might be beneficial for the management of this increasing proportion of individuals who come to the ED.

**Trial registration:** (Trial registration number: ClinicalTrials.gov NCT05753319). https://classic.clinicaltrials.gov/ct2/show/NCT05753319.

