Briefly, patients aged 75 years and over admitted with a chief complaint of a ‘fall’ are first clinically assessed within the EU, to provide a prompt clinical exam, an initial course of action, and an initial decision for orientation. After this first stage, there are three possibilities: (i) the situation is benign and the patient is discharged; (ii) there is a clear indication for hospitalization; or (iii) the clinical situation is unpredictable and the patient can be admitted to the OU for observation/monitoring, treatment, and further assessments. As illustrated in Fig 3, the typical pathway involves patients initially going to the EU where they may be directed to one of the three options: returning home, being hospitalized (in another unit of the hospital), or being transferred to the OU. Once in the OU, these patients may later be directed to either return home or continue hospitalization.

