### Data analysis and interpretation

An independent statistician will perform will perform the analyses (SAS, 9.4^®^).

A review of data will be conducted at the end of the study, prior to statistical analysis. The aim will be to review the progress of the study, potential problems and classify any minor or major deviations. Analyses will be performed in the *Intention-to-Treat* populations corresponding to all randomized patients. A sensitivity analysis will be conducted on the *Per-Protocol* population. This population will include patients without major deviation.

The variables measured at baseline will be described for all patients in both groups by numbers and percentages for each category for categorical variables and the minimum, maximum, average, standard deviation and quartiles for the quantitative variables. (Table 2).

Primary endpoint: the patient orientation at discharge from the ED will be described and compared between the two groups with Chi-square tests, depending on the ED unit of inclusion (emergency unit: 3 modalities: discharge home, hospitalization, observation unit; observation unit: 2 modalities: discharge home, hospitalization).’

Secondary endpoints: LOS-ED and LOS-hos will be described as mean difference and 95% confidence intervals, and compared between the groups using Student’s t tests. The rate of re-visits to ED for fall complaints (characterized as a new episode of fall whose severity requires a re-hospitalization within 7 days) will be compared between groups using Chi-square test. The changes in the patient’s orientation between initial and final decisions will be compared between the groups using Chi-square test. Satisfaction of ED medical staff will be depicted descriptively.

Due to this ‘pragmatic’ approach, it is not possible to compute a priori statistical calculations. The distribution of patients within both units of the ED (EU or UN), the different modalities of patient discharge (Fig 3), and for each group (PT vs no-PT) make it challenging to determine expected differences between groups for the main outcome. As stated, we aim to recruit, as exhaustively as possible, during the inclusion period.

Any missing data will be described and explained. There will be no imputation done on missing data.

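### The primary endpoint treats transfer to the observation unit as an end category, so no primary test compares final home-or-hospital disposition in all randomised patients

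*Protocol article*

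**What the plan says.** - **Objective.** Abstract: "The main objective is the evaluate the effect on the discharge disposition (discharge home, hospitalization". The Introduction states it more loosely, as discharge disposition after the ED visit.
- **Role of the OU.** Study setting describes the OU as a place for observation, treatment and further assessment: "Once in the OU, these patients may later be directed to either return home or continue hospitalization". Data analysis and interpretation counts it as part of the ED: "The distribution of patients within both units of the ED (EU or UN" (the second abbreviation is evidently the OU).
- **Primary outcome.** Outcomes lists orientation at ED discharge as "return to home (after ERU or SSHU), hospitalization (after ERU or SSHU) or SSHU (after ERU". I read ERU and SSHU as the EU and OU. Table 2 supports this by giving SSHU as the third destination of EU patients.
- **Primary test.** Data analysis and interpretation plans Chi-square tests "depending on the ED unit of inclusion (emergency unit: 3 modalities: discharge home, hospitalization, observation unit; observation unit: 2 modalities: discharge home, hospitalization".
- **Table 2.** It has two separate blocks, "Orientation, at discharge from ED (EU patients" and "Orientation, at discharge from ED (OU patients", and no row that pools home and hospitalization over both.
- **Other rules that bear on this.** The analysis population is all randomised patients. Randomisation is 1:1 and not stratified. The intervention runs daily until ED discharge, and the physiotherapist's recommendation is available for the physician's final orientation decision.

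**The concern.** If the question is whether PT changes who goes home and who is hospitalized, moving from the EU to the OU does not answer it. The patient is still in the ED and the decision is still open. Study setting presents the OU as the place where a first decision can be revised, and the final decision is the one that the physiotherapist's recommendation is meant to inform.

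Two things are at stake. A PT effect that arises after transfer to the OU can be missed by the primary analysis. A change in transfers alone can also produce a positive primary result while the proportion finally going home is the same in both arms.

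**Working it through.** **Step 1: trace each pathway through the plan's rules.** The split is taken as unit of inclusion.

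| Pathway | Categories it fits in Outcomes | Where it is tested | Final disposition in a primary test? |
|---|---|---|---|
| Included in EU, then home | home | EU table, home | yes |
| Included in EU, then hospital | hospitalization | EU table, hospitalization | yes |
| Included in EU, then OU, then home | home (after OU) and OU (after EU) | EU table, observation unit | **no** |
| Included in EU, then OU, then hospital | hospitalization (after OU) and OU (after EU) | EU table, observation unit | **no** |
| Included in OU, then home or hospital | home or hospitalization | OU table | yes |

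Rows three and four each fit two outcome categories, and no rule says which one counts. In the test they fall under observation unit.

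**Step 2: inputs for the size.** From the article: 336 patients, 1:1, so 168 per arm. The article gives no EU-to-OU transfer rate and no expected effect. My assumptions are two-sided 5%, all patients included in the EU, a transfer share q of 20% to 80%, and half of patients going home without PT from either unit.

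Patients whose final disposition is outside the EU test number 336 × q: 67, 134, 202 and 269 for q = 20, 40, 60 and 80%.

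**Step 3: PT acts only in the OU (home 50% to 70% there).** Transfers and direct discharges are the same in both arms, so the EU table has the same expected proportions in both and rejects at 5%. That follows from the assumption. What matters is what a test of final disposition would have seen. Final home is 50% against 50% + 20% × q. Power is Φ[(d − 1.96·SE0)/SE1], where d is the difference, SE0 the pooled and SE1 the unpooled standard error.

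| q | Final home, no PT vs PT | EU three-category test rejects | Final-disposition test, all 336 |
|---|---|---|---|
| 20% | 50% vs 54% | 5% | 11% |
| 40% | 50% vs 58% | 5% | 31% |
| 60% | 50% vs 62% | 5% | 60% |
| 80% | 50% vs 66% | 5% | 85% |

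**Step 4: PT changes only the transfers.** Control proportions in the EU table (home, hospital, OU) are 30/30/40. With PT they are 25/25/50 or 22.5/22.5/55. Half of the transferred patients go home in both arms, so final home is 50% throughout. The noncentrality is the sum over arms and categories of 168·(p − p̄)²/p̄, on 2 degrees of freedom.
- 40% to 50%: noncentrality 3.39, rejection in 36% of trials.
- 40% to 55%: noncentrality 7.58, rejection in 69% of trials.

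**Step 5: the looser reading of Table 2.** Suppose OU patients means anyone who reached the OU. A transferred patient then appears in both blocks, and the OU comparison is made in a group formed after randomisation. Take controls with 40% in the OU, half of them going home (20% of all). Suppose PT sends 8% of all patients straight home who would otherwise have gone home through the OU.
- Final disposition is unchanged.
- OU share with PT: 40% − 8% = 32%. Home among them: (20% − 8%)/32% = 37.5%, against 50% in controls.
- With about 67 and 54 patients, noncentrality is 1.89 on 1 degree of freedom: rejection in 28% of trials, in the direction of harm.

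The direction is not general. If PT also turns 4% of all patients in the OU from hospital to home, OU home becomes (12% + 4%)/32% = 50%. The OU table shows no difference, although final home has risen by 4 points.

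A latent-severity simulation agrees. It assumed that controls split 29% home, 45% OU and 26% hospital, with a PT shift of 0.4 SD. With the shift in the EU only, OU hospitalization is 52% in controls against 59 to 84% with PT, as the noise in the OU decision runs from 2 to 0 SD. With the shift in both units (noise 0.3 to 1.0 SD), it is 52% against about 48 to 51%, while final hospitalization falls from about 50% to 35–36%. The effect is masked, but it does not look like harm.

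**The case against.** **The split is by a baseline attribute.** The analysis section says unit of inclusion. This is correct and favours the first reading. The post-randomisation problem rests only on the shorter labels in Table 2 and is conditional on them.

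**Patients included while in the OU are properly handled.** Correct. For them the test is already home versus hospitalization within a baseline subgroup.

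**Outcomes does count home and hospitalization after the OU, and the change from initial to final orientation is a secondary endpoint.** Both are true, so final disposition is recorded and a change of decision in the OU is not wholly lost. But the test described does not use the post-OU result of EU-included patients, and a comparison of changes is not a comparison of final dispositions.

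**The two-category objective stands only in the abstract, and one sentence in Study setting places the OU near the ED rather than in it.** If transfer were an exit from the ED, three destinations would be coherent. However, the analysis section counts the OU as an ED unit, and Study setting has its patients still awaiting home or hospital. That PT continues in the OU is likewise an inference from its running until ED discharge. Figures 2 and 3 and the full protocol are not shown and might clarify the flow.

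**Stronger readings to avoid.** A reader might infer that many patients lose their outcome. The article gives no transfer rate, so that cannot be said. A reader might also infer that the OU table would show PT as harmful. That needs the looser Table 2 reading and particular scenarios, such as an effect confined to the EU.

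**Conclusion.** The concern holds in a limited form. As written, the primary test scores EU-included patients who move to the OU by an intermediate step, and no primary test compares final home versus hospitalization in all randomised patients, which is the objective in the abstract. The outcome definition also lets these patients fit two categories. This conclusion comes from the text and needs no assumed figure.

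Its size is not known. Under the assumptions in the working, 67 to 269 of 336 patients would be scored this way for transfer shares of 20% to 80%. An effect confined to the OU would be missed by the EU test, and a 10-point shift in transfers would make that test positive in about 36% of trials with nothing changed in final disposition. Bias and double counting in the OU table are an additional risk only if Table 2 means everyone who reached the OU.

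It should be corrected before analysis, because it determines what the primary result means.

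**What to change.** Define one primary outcome for every randomised patient: final disposition on leaving the ED pathway, whether from the EU or the OU, as home versus hospitalization. Compare it once in all randomised patients, as randomised, with a risk difference and 95% confidence interval. Report transfer to the OU and the three-category EU orientation as secondary or descriptive results. State that any split by unit, including the two blocks of Table 2, uses the unit recorded at randomisation.

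With 168 per arm and an assumed 50% going home without PT, this test has 45% power for 60% home, 80% for 65% and 97% for 70%. The article gives no target difference to set against these.

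The cost is wording in the protocol, the analysis plan and Table 2. Orientation is a record-based outcome already, so no new data collection is needed. The downside is that OU transfer leaves the primary test. If the investigators regard it as important in its own right, it can be a named secondary outcome.

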## Materials and methods

### Study design

This is a prospective open-label, randomized, monocentric, two-arm parallel controlled trial to analyse the effects of the delivery of PT in ED, for patients aged 75 years and over, admitted for ‘fall’ chief complaint. The study is reported according to the Standard Protocol Items: Recommendations for Interventional Trials (SPIRIT) [30]. The SPIRIT diagram and flowchart for participants are provided in Figs 1 and 2, respectively.

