### Dissemination

The results of this study will be disseminated to through our and neighbouring EDs, and through professional emergency and physiotherapy networks and faculties (e.g., lectures). We will also apply to present the trial results at conferences among these fields. Scientific written reports of the findings will conform to the Consolidated Standards of Reporting Trials (CONSORT) statement guidelines. The publication authorship will be determined based on the International Committee of Medical Journal Editors (ICMJE) guidelines. We intend to publish in a reputable non-predatory journal, selecting the most relevant one in using emergency and/or physiotherapy related-categories based on SCImago Journal ranking. We may also considerate the necessity of engaging a professional medical writer.

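### Seven-day re-visits are fall-only and taken from the medical record, and the 7-day call is stated to collect falls, so returns to other hospitals are probably missed and non-fall returns reach no outcome

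*Protocol article*

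**What the plan says.** The trial is a "prospective open-label, randomized, monocentric, two-arm parallel controlled trial" (Study design). After listing length of stay and "the number of re-visits to ED for fall complaints (within 7 days", the Outcomes section states: "These outcomes will be found from the medical record of the patient". It then says that an investigator will "call the patient (phone) after 7 days to collect the number of falls since discharge from ED (follow-up". No other content of the call is given.

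Table 2 has the row "Number of re-visits to ED for falls, within 7 days" and a row for falls. It has none for return for any cause, unplanned admission or death.

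Data analysis and interpretation compares the re-visit rate between arms with a Chi-square test, but there a re-visit is "characterized as a new episode of fall whose severity requires a re-hospitalization within 7 days".

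The primary outcome is orientation at ED discharge. Under Intervention, the physiotherapist in the PT arm gives a recommendation on discharge or hospitalization, which the emergency physician can use for the final decision.

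**The concern.** The intervention is designed to feed into disposition. If it increases discharge home, readers will want to know whether those patients come back. Two kinds of return seem to escape the re-visit endpoint:

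- A patient who goes to a different hospital's ED probably leaves no trace in the record used.
- A patient who returns for a reason not labelled a fall, or who is admitted unplanned for such a reason, falls outside the definition wherever care is sought.

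Patients sent home have more opportunity to return within 7 days than patients still in a hospital bed. The gap therefore lies in the group whose size the intervention may change. The Introduction itself lists ED revisits with later hospitalization, alongside recurrent falls, as adverse events in this population.

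**Working it through.** The point is mainly one of reading. The documents state no re-visit rate, capture rate, alpha or power, so there is no figure to reproduce.

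**Which source sees which event**

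| Event within 7 days | Medical record, as a re-visit | 7-day call, as stated |
|---|---|---|
| Return to this ED for a fall | Yes under Outcomes; under Data analysis only if re-hospitalization is required | Fall counted |
| Visit to another ED for a fall | Probably not | Fall may be counted, but not as a re-visit |
| Return to this ED for a non-fall reason | Outside the definition | Not asked |
| Visit to another ED for a non-fall reason | Outside the definition, and probably not seen | Not asked |
| Unplanned admission for a non-fall reason | Outside the definition | Not asked |

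The second row is under-ascertainment of the stated endpoint. The last three are limits of what the endpoint measures. The two should be kept apart. The first row also shows that the two sections do not define the same event.

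**Scale of under-ascertainment (all rates assumed)**

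Inputs from the document: 336 patients (Abstract) at 1:1 (Allocation), so n = 336 / 2 = 168 per arm. Assumed: two-sided alpha 0.05, true risks p1 and p2 = 2 × p1, and a fraction c of returns captured equally in both arms.

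Observed risks are a = c × p1 and b = c × p2, with mean m = (a + b) / 2. Expected events are n × (a + b). Power = Φ{[(b − a) − 1.96 √(2m(1 − m)/n)] / √[(a(1 − a) + b(1 − b))/n]}.

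For 5% versus 10%:

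| c | Expected events | Observed difference (points) | Power |
|---|---|---|---|
| 1 | 168 × 0.15 = 25.2 | 5.0 | 0.41 |
| 0.75 | 18.9 | 3.75 | 0.32 |
| 0.50 | 12.6 | 2.5 | 0.23 |
| 0.25 | 6.3 | 1.25 | 0.13 |

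Going from full to half capture, power falls from 0.26 to 0.15 for 3% versus 6%, and from 0.73 to 0.41 for 10% versus 20%.

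**Does this favour the PT arm?**

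Assume home discharge of 50% without PT and 60% with it, a return risk of 8% for those sent home, and none otherwise (a simplification).

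- True risks: 0.5 × 0.08 = 4.0% and 0.6 × 0.08 = 4.8%. Expected returns are 168 × 0.040 = 6.7 and 168 × 0.048 = 8.1.
- With 75% capture in both arms: 3.0% and 3.6%. The difference falls from 0.8 to 0.6 points; the ratio stays at 4.8 / 4.0 = 3.6 / 3.0 = 1.2.
- Missed returns: 0.25 × 6.7 = 1.7 and 0.25 × 8.1 = 2.0.

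Equal capture shrinks the difference and leaves the ratio alone. A stronger distortion needs capture to differ between arms, and nothing in the document shows that it does.

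**The case against.** The strongest reply has four parts.

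- **The call is already a post-discharge check.** A reader might infer that the re-visit endpoint is the only safeguard against unsafe discharge. It is not. The telephone fall count does not depend on where care was sought, and falls within 7 days are a named secondary objective. The section on adverse events also lets investigators report any event, though it describes no active collection after discharge. This part stands, but the call as stated covers falls alone.
- **A fall-specific endpoint suits the trial.** The patients are fallers and the intervention targets balance and gait. This stands too. Replacing the endpoint with an all-cause one would be a debatable choice, not a correction.
- **The local record and the narrow call are inferences.** The article refers to the patient's record without limiting it to this centre, and it does not say that the call excludes other questions. The full protocol (S4 File) is not shown. This lowers certainty about visits elsewhere. It does not remove the non-fall gap, because the article itself fixes the endpoint as fall-related.
- **Neighbouring EDs prove little.** The phrase "through our and neighbouring EDs" comes from Dissemination. It shows that such departments exist, not that trial patients use them.

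**Conclusion.** The concern holds as a limited weakness in one secondary outcome. It does not touch the primary outcome or its analysis. Fall-related visits to other hospitals would probably not be counted as re-visits, and non-fall returns and unplanned admissions are in no listed outcome. The first statement rests on reading the record as this hospital's; the second follows from the stated definitions.

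Two stronger readings are tempting but unsupported:

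- **The gap makes PT look safer than it is.** This is plausible, since more patients sent home means more opportunity to return. But hospitalized patients can also be discharged and return within 7 days, and the documents give neither lengths of stay nor capture by arm. Neither the size nor the direction of any bias can be derived.
- **Most returns are lost.** If 20–40% went elsewhere and half of returns were not labelled falls, the combined loss would be 1 − 0.8 × 0.5 = 60% to 1 − 0.6 × 0.5 = 70%. Every input is assumed, and the product mixes missed endpoint events with events the endpoint was never meant to count.

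The power figures above are likewise only for scale. Even with full capture, 168 per arm gives 0.41 for an assumed doubling from 5%, so better ascertainment removes an avoidable loss without making this comparison well powered.

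**What to change.** 1. In the existing 7-day call, also ask about any ED visit or unplanned admission since leaving the ED, at any hospital, with the reason.
2. Keep fall-related re-visits as the stated secondary endpoint, counted from the call and the record together.
3. Give it one definition. Outcomes describes an ED re-visit for a fall and Data analysis a fall requiring re-hospitalization; these must be reconciled before analysis.
4. Report return or unplanned admission for any cause, by arm, as an added safety outcome.

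The cost is one or two questions in a call already planned, a revised definition and one more row in Table 2. The downsides are that visits elsewhere rest on self-report and that all-cause returns include some unrelated events, which is why the fall-related endpoint should be kept beside them.
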